### Assessments

In this study, therapeutic efficiency will be assessed in terms of the following aspects: cognitive performance, fatigue, QoL, and chemotherapy-induced side effects. The primary outcome of this study is to verify whether EA is therapeutically useful for preventing chemobrain and alleviating the related symptoms and the safety of intervention. Cognitive performance will be assessed using MoCA + FACT-Cog. The secondary outcomes are as follows: QoL will be measured using EORTC QLQ-C30, fatigue will be assessed using the FACIT-Fatigue scale, and the manifestation of chemotherapy-induced side effects will be assessed using the Chemotherapy Symptom Rating Scale FAACT + FACT-BRM. All assessment scales will be evaluated by previously trained researchers at the following timepoints (see Figure 2): baseline (T0), midpoint of main treatment (T1-T3) once every 2 weeks, and end of the 8-week main treatment (T4) (a total of 5 timepoints). We will also keep a record of all the shedding cases. This study is a multidisciplinary clinical trial (across oncology and Chinese medicine disciplines) on the role of Chinese acupuncture as therapy for chemotherapy-induced cognitive impairment in older patients with cancer. If successful, findings from this study might have beneﬁts in reducing chemotherapy-induced working memory impairment. Data from this study may be used to support an implementation and dissemination trial of Chinese EA in real-world behavioral health and social service settings.

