#### Sample Size Estimation

A total of 168 older patients with cancer will be recruited, of which 84 will be in the experimental group (EA) and 84 will be in the control group. Sample size calculation:

n = [p1 (1 – p1) + p2 (1 – p2)]/(p1 – p2)] × Cp.power

Cp refers to the process capability index. In the 2-sided test, Cp.power = 10.5 when *P*<.05 is met. n is the number of patients to be recruited in each group, p1 and p2 represent the incidence in each group, and a mean difference with 95% level of significance (α) and 80% power (1 – β) is set. In older patients with cancer, the incidence of chemobrain after chemotherapy is 30%, and the reduction of chemobrain could be 10%-20% with acupuncture intervention. The sample size for each group is 84 participants, considering a 20% dropout. Therefore, the overall target sample size of 168 will be included.

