### Statistical Analyses

Cognitive impairment is defined as those with SD>1.5 in the mean scores of MoCA and the QLQ-C30 at baseline for all participants at different timepoints. A time-series test in the Kaplan-Meier survival analysis will be used to compare the incidence of cognitive deficits accumulated after 8 weeks of acupuncture intervention between the 2 groups. Linear mixed-effects modeling will be used to compare participants’ cognitive impairment, fatigue, and depression at baseline, during, and after acupuncture intervention, where only those who have completed at least one assessment at baseline and during treatment will be compared. This model will use time and group as categorical fixed factors and random intercepts and use random intercepts in conjunction with a measurement covariance matrix. Participants’ age, chemotherapeutic drug dosage, fatigue at baseline, depression, and additional treatments will be considered as covariates in the statistical analyses. A 2-sided *t* test will be used to compare the covariates at each timepoint between the 2 groups. The chi-square test will be used for qualitative information and the *t* test will be used for continuous information at baseline. Statistical significance will be considered at *P*<.05. The study data used will be statistically analyzed using SPSS software (IBM Corp) under the supervision of a statistician. To ensure the privacy of the patients, all relevant study data and personal data will be kept in a locked file cabinet. Electronic data will be stored on an encrypted computer and will not be stored on any external storage device. Each participant will be assigned his or her own ID in the study record, which will be used in lieu of his or her name and personal identifying information. Clinical data from the study will be kept in a separate file from the participant’s personal data. The principal investigator will be responsible for all the clinical trial data. During and after the clinical trial, the principal investigator, researchers, and the ethical review committee have the right to view the study data. Participants will have the right to access their personal data and the results of the study. All study data will be stored for a minimum of 3 years after the completion of the trial, after which they will be destroyed in accordance with the rules of the ethics review committee.

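### In the fatigue mixed model, baseline fatigue is both a response visit and a covariate, and no group-by-time term is named; read literally, the arm effect is diluted by about 20% or collapses to zero

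*Protocol article*

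**What the plan says.** All of this is in the Statistical Analyses section of the protocol article unless noted.

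- The mixed model compares "cognitive impairment, fatigue, and depression at baseline, during, and after acupuncture intervention". Baseline fatigue is therefore one of the modelled responses. The Assessments section gives "a total of 5 timepoints", so that is one baseline visit and four later ones.
- On fixed effects: "This model will use time and group as categorical fixed factors and random intercepts". No group-by-time interaction is named.
- On covariance, the model will "use random intercepts in conjunction with a measurement covariance matrix". The structure of that matrix is not named.
- On adjustment: "age, chemotherapeutic drug dosage, fatigue at baseline, depression, and additional treatments will be considered as covariates". The list applies to the statistical analyses in general, and the fatigue model is not exempted.
- Fatigue is a secondary outcome: "fatigue will be assessed using the FACIT-Fatigue scale" (Assessments).

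**The concern.** In the fatigue model the same number stands on both sides of the equation at the baseline visit. In addition, a single group effect is asked to describe five visits, at one of which randomization makes the true difference zero. These are two different faults with different consequences, and they should be kept apart.

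At stake is the estimate for one secondary outcome. An analyst who follows the printed specification would report a real fatigue benefit as smaller than it is, with an interval that misses the true value too often. Under some covariance choices the model would not fit, or would return zero.

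**Working it through.** **Inputs.** From the article: five visits, of which one is baseline; 84 per arm, reduced by the stated 20% dropout to 84 × 0.8 ≈ 67; fixed factors time and group. Assumed, because the article gives no figures: SD 1 at each visit, true effect d = 0.40 SD at all four later visits, equal correlation r = 0.5 to 0.85 between visits, complete data. The article states no fatigue effect, so there is no figure of its own to reproduce.

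**1. Constant-variance random intercept: dilution.** With balanced data the group effect is estimated from each patient's mean over the five visits, M = (Y0 + 4P)/5, where P is the mean of the four later visits.

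- Regressing M on group and Y0 gives a group coefficient of 0.8 × the ordinary baseline-adjusted estimate for P, which is 0.8 × 0.40 = 0.32. The slope on Y0 is 0.2 + 0.8r.
- Regressing M on group alone gives (0 + 4 × 0.40)/5 = 0.32 as well. So the covariate does not cause the 20% loss.

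**2. What the covariate does to the interval.** The bias is 0.08 in both versions; only the standard error differs.

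- With the covariate: SE = 0.8 × √(2v/67), v = (1 + 3r)/4 − r².
- Without it: SE = √(2u/67), u = (1 + 4r)/5.
- Coverage = Φ(1.96 − b) − Φ(−1.96 − b), with b = 0.08/SE.

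| r | SE with | b | coverage with | SE without | b | coverage without |
|---|---|---|---|---|---|---|
| 0.50 | 0.085 | 0.95 | 84% | 0.134 | 0.60 | 91% |
| 0.70 | 0.074 | 1.08 | 81% | 0.151 | 0.53 | 92% |
| 0.85 | 0.056 | 1.43 | 70% | 0.162 | 0.49 | 92% |

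Several sets of simulations with the covariate gave coverage between 68% and 88%, in line with this algebra.

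**3. AR(1) errors.** Fits to data with exactly matched moments (84 per arm, effect 0.5 SD, constant or rising linearly) gave 0.70 to 0.80 of the true mean post-baseline effect, a loss of 20 to 30%.

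**4. Variance allowed to differ by visit: collapse.** The model for the baseline row is Y0 = time effect + β × group + γ × Y0 + error. Setting γ = 1, β = 0 and the baseline time effect to 0 makes every baseline residual zero. The baseline variance can then shrink towards zero and the log-likelihood rises without limit. Because β is shared by all visits, it is held at zero everywhere.

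- One iterated unstructured fit: over 14 iterations the baseline residual variance went from 0.13 to 3 × 10⁻¹¹, the slope from 0.64 to 1.00, the group effect from 0.177 to 0.000, and the log-likelihood from −640 to +839.
- In 120 unstructured fits with a true effect of 0.40, the group estimate was zero with slope 1 every time.
- A random intercept plus visit-specific variances also gave 0.00.
- With baseline as a response but not a covariate, the unstructured fit gave 0.66 to 0.80 of the truth, not zero. The collapse, unlike the dilution, is due to the double use.

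**5. With a group-by-time term.** Change-from-baseline contrasts were 1.00 of the truth under every structure tried. Under a constant-variance random intercept the slope stayed at 0.2 + 0.8r, that is 0.60 to 0.88. Only under visit-specific variances was it forced to 1. The week-8 contrast then equals the plain change score, with (1 + r)/2 of the information of baseline adjustment: 75 to 85% for r = 0.5 to 0.7.

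**6. Baseline as covariate only, responses at weeks 2 to 8.** With a constant effect the estimate was about 0.40, with 92 to 97% coverage.

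**The case against.** The strongest case against runs as follows.

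- The article says only that covariates will be considered, in one list shared by several outcomes. Fatigue and depression are natural adjusters for cognition, and a full analysis plan could drop baseline fatigue from its own model. **This stands as a condition.** Use in the fatigue model is the natural reading, but it is not spelled out.
- An interaction is not excluded, and covariance structures are commonly left to the full plan. **This stands in part.** The omission alone would be no finding. But the article does commit to named fixed factors, to baseline as an occasion and to baseline fatigue as a covariate, and those commitments conflict.
- An unstructured matrix is not identifiable beside a random intercept, so that example is an unlikely reading. **This is fair,** but visit-specific variances beside a random intercept collapse in the same way.
- A fit that fails or returns exactly zero would be noticed by the supervising statistician. **This is likely** for the collapse. It does not help with the dilution, which looks like an ordinary result.

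A reader might infer that the double use causes the 20% loss. It does not: the loss is the same without the covariate. A reader might also infer that a group-by-time term is no cure. It does remove the bias in the contrasts, and the forced slope belongs only to visit-specific variances.

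**Conclusion.** The point holds for the fatigue outcome as specified in the article, conditional on two things: baseline fatigue is entered in the fatigue model, and no group-by-time term is fitted.

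On that reading the group effect is about 20% too small with a constant-variance random intercept and 20 to 30% too small with AR(1). The covariate lowers coverage further, to about 68-88% under the random intercept. If variances may differ by visit, the fit fails or returns zero. The coverage figures rest on the assumed effect, correlations and complete data. The 20% follows from one visit in five carrying no effect. The collapse follows from the algebra.

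It would be too strong to say that the trial will report a null fatigue effect, since the article does not name the covariance matrix. It would also be too strong to extend the point to the primary cognitive analysis, where baseline fatigue is not the response. Depression is likewise both outcome and covariate, but the text does not say that the covariate is its baseline value.

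The correction should be made before analysis. It concerns a secondary outcome and does not threaten the trial as a whole.

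**What to change.** In the fatigue model, use weeks 2, 4, 6 and 8 as the responses and keep baseline fatigue as the covariate. If baseline is to stay as a response, drop it as a covariate and test treatment through the group-by-time contrasts; dropping the covariate alone leaves the dilution in place.

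Add a general rule that no outcome's baseline value may be both a response and a covariate in one model, and name the group-by-time term and the covariance structure. Naming the contrast matters under the first option too. If the effect rises over the visits, a single group effect need not equal the plain average of the post-baseline effects. With an unstructured matrix it gave 0.77 and 0.82 of that average for the two data types with autoregressive correlation, and 1.00 with equal correlation.

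The cost is one or two sentences in the analysis section. No data collection changes and no patient is affected.

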## Results

This clinical trial was funded by the Jiangsu Health Vocational College and Nanjing First Hospital in January 2023. The ethics review committee approval was finalized in April 2023, and data collection began on September 1, 2023. Investigators have since been engaged in activities associated with study enrollment and data collection, including recruitment, screening, consenting, and enrolling participants; administering EA intervention; timepoint assessing; and monitoring adverse events and resolving problems early. As of October 21, 2023, 11 participants have been recruited into the clinical trial. A total of 168 older patients with cancer who are undergoing or are just about to commence chemotherapy will be enrolled in this clinical trial, and they will be randomly assigned into either the experimental group or the control group of 84 participants each. A total of 16 EA treatments (twice per week) will be administered to each participant for 8 weeks, and the participants will be assessed for cognitive performance, fatigue, and QoL. Concurrently, they will receive conventional chemotherapy. Improvement or even relief of chemobrain symptoms in older patients with cancer undergoing chemotherapy will be expected if the results of the EA intervention are satisfactory.

## Discussion

Patients with cancer may have concerns of psychiatric and digestive symptoms while undergoing or just after having recently undergone chemotherapy [3]. The most common clinical manifestations are fatigue, nausea, vomiting, dry mouth, anxiety, depression, and insomnia. More seriously, cognitive impairments with a range of neurocognitive symptoms occur frequently, including visual and verbal memory impairment, forgetfulness, difficulty concentrating, learning difficulties, and organizational and coordination dysfunction [3,4]. Since the 1980s, researchers have been studying chemotherapy-induced cognitive impairment and have given several definitions to this condition, such as postchemotherapy cognitive impairment and chemotherapy-induced cognitive dysfunction. Recently, this condition was termed as chemobrain [3-5].

Chemobrain is a frequent side effect experienced by an increasing number of older patients with cancer, and it has significantly impacted their QoL [4]. Chemobrain can be described as cognitive symptoms reported by patients with cancer in self-reported questionnaires or as cognitive changes evaluated by formal neuropsychological tests [5]. Older patients with cancer will experience cognitive impairment due to chemoradiotherapy, which will lead to a series of neurocognitive symptoms called chemobrain. Older populations have been disproportionately affected by chemobrain and have heightened negative mental health outcomes after cytotoxic chemical drug therapy [3,5,7].

According to available literature [3,14], more than 75% of patients with cancer experience cognitive impairment while undergoing chemotherapy or just after completing chemotherapy, with 15%-30% of these patients experiencing persistent symptoms for up to decades. The prevalence of postchemotherapy cognitive impairment is as high as 50%-75% among older cancer survivors [33]. In some circumstances, the cognitive impairment can be lifelong, affecting the patient’s mood, relationships, QoL, career, social activity, and family life. Considering the increasing incidence of cancer, chemobrain is quite complicated, increasingly important, and has far-reaching consequences. As the incidence of cancer survivors rises, the adverse effects of chemobrain will become more frequent, thus necessitating the need to effectively prevent and treat chemobrain.

At present, there is no responsive therapy for chemobrain. The current clinical medications are not effective for chemobrain prevention and therapy. Study and research literatures [14,15] suggest that Chinese acupuncture might be effective for relieving various discomforts caused by anticancer drugs, such as pain, vomiting, fever, fatigue, dry mouth, anxiety, depression, and sleep disorders. Several studies [11,13-16,30] have shown the efficacy of EA intervention in various neurological diseases. Compared with acupuncture, EA has reported to produce a higher intensity of stimulation on acupoints and is progressively being widely used for its adjustable strength, frequency, and easy quantification in clinical practice [14]. In addition, EA can promote the rehabilitation of pathological microstructures in the brain and improve the cognitive function of patients with cognitive impairment [16].

Our study aims to explore the feasibility, efficacy, and safety of using EA by involving multiple disciplines (oncology and Chinese Medicine) to treat chemobrain in older patients with cancer. Acupuncture itself has been demonstrated as a safe and effective treatment, and EA is a widely accepted and cost-effective alternative therapy option with low adverse effects for older patients with cancer. The findings of this study will provide useful information on determining a suitable therapy for chemobrain in older patients with cancer. EA may be ready for implementation and dissemination in real-world cognitive function settings consistent with the objectives outlined in this clinical trial’s strategic plan. Overall, this proposal has the potential to decrease neurocognitive symptoms among older patients with cancer—populations determined to be most at risk of exacerbated, long-lasting negative health sequelae. EA, if proven to be effective, can be implemented into routine settings to benefit older patients with cancer experiencing chemobrain. We believe that data from this efficacy trial will determine whether Chinese EA successfully alleviates the symptoms of chemobrain and whether these improvements could markedly reduce the various side effects due to cytotoxic chemical drugs.

In conclusion, the goal of this clinical trial is to target and reduce emerging and likely exacerbated cognitive impairments caused by chemotherapy among older patients with cancer. We aim to evaluate this novel Chinese medicine mode of EA in older patients with cancer by developing a therapeutic responsive treatment for chemobrain. By addressing neurocognitive symptoms through an EA intervention that targets underlying pathophysiological and psychological factors, we hope that this EA intervention will reduce the symptoms of chemobrain in older patients with cancer. If successful, findings from this study might have beneﬁts in reducing chemotherapy-induced working memory impairment. Data from this study may be used to support an implementation and dissemination trial of Chinese EA within real-world behavioral health and social service settings.

## Abbreviations

EA: electroacupuncture
EORTC QLQ-C30: European Organization for Research and Treatment of Cancer Quality of Life Questionnaire-Core 30
FAACT: Functional Assessment of Anorexia-Cachexia Therapy
FACIT-Fatigue: Functional Assessment of Chronic Illness Therapy-Fatigue
FACT: Functional Assessment of Cancer Therapy
FACT-BRM: Functional Assessment of Cancer Therapy-Biologic Response Modifier
FACT-Cog: Functional Assessment of Cancer Therapy-Cognitive function
MoCA: Montreal Cognitive Assessment
QoL: quality of life
STRICTA: Standards for Reporting Interventions in Clinical Trials of Acupuncture
